### 5. Procedures to be followed

Potentially interested participants will call a toll-free number and speak to a study coordinator, who will complete a phone screener. The phone screener includes questions in the following categories: basic demographic information, race and ethnicity, exclusion criteria questions, contact information (e.g., phone number) and social security information, so that we are able to mail compensation for participation in the study. Data from this phone screening process will be collected on paper and parts of this form will be later entered into the management module. During this phone screener, the study coordinator will explain the study, ask questions to determine eligibility and then ask once again if the patient may be interested in participating. If the participant is eligible and interested, the study coordinator will read the verbal consent document over the phone. If the participant is interested, eligible and consents to participate in the study over the phone, the study coordinator will inform the participant that he/she is included in the study and will receive an email within the next day from the study, explaining what will happen next. The coordinator will also inform the participant that upon logging into the application for the first time, they will have to read, review, and electronically agree to a Member Authorization Form by Highmark. They will be able to print out this form for their own records. Those that do not agree will not be allowed to participate. Those that do agree will then be randomized automatically, according to an algorithm written in the management module, to either the asthma or preventive care modules. The study coordinator will enter the specific screening information into the application (all screening fields except for mailing address and SSN) after their phone call with the participant and then check a box representing that the participant has completed the phone consent procedure. The participant will then be asked to use the website once every 30 day cycle and within 14 days of their next scheduled visit with their asthma care provider. At baseline, 6 months, and 12 months, they will be asked to complete specific measures online, as outlined below. During other monthly logins, they will be asked to complete short surveys that will then generate feedback based on their group they were randomized to. Women of child bearing potential will be asked monthly if they are currently pregnant and if they state that they are, they will be withdrawn from the study. At the close of the study, Penn State researchers will be authorized to provide Highmark with the names, DOB’s, gender and dates participants electronically agreed to the Member Authorization Form. Highmark will then provide Penn State researchers with access to claims data for all enrolled participants, for the 2 years prior to study participation and up to 2 years post enrollment. Asthma-related claims of hospitalization, outpatient visits, emergency department visits and medications will be examined.

|  | Phone Screener | Base | Every 30 days | CYCLE 6 | CYCLE 13 | Claims |
| --- | --- | --- | --- | --- | --- | --- |
| Age, gender, race, ethnicity (5) | X |  |  |  |  |  |
| Exclusion (smoking amount, Internet access, asthma history, English fluency)(10) | X |  |  |  |  |  |
| Contact and payment information (13) | X |  |  |  |  |  |
| Demographics, height, weight, QOL (14) |  | X |  |  | X |  |
| Asthma Control Test (5) |  | X |  | X | X |  |
| Asthma Control and Quality of Life (11) |  | X |  | X | X |  |
| Health Conditions (14) |  | X |  |  |  |  |
| Patient Satisfaction Questionnaire (19) |  | X |  |  | X |  |
| Patient Involvement (5) |  | X |  |  | X |  |
| Health Literacy (2) |  | X |  |  | X |  |
| Internet Use (29) |  | X |  |  | X |  |
| Asthma Counseling (5) |  | X |  |  | X |  |
| Newest Vital Sign (8) |  | X |  |  |  |  |
| CC Condition Pre-Use Questions (27) |  | X | X* |  | X |  |
| IC Condition Pre-Use Questions (16) |  | X | X* |  | X |  |
| Emergency department visits |  |  |  |  |  | X |
| Medication use and adherence |  |  |  |  |  | x |
| Outpatient provider visits for asthma |  |  |  |  |  | X |
| Adverse events |  |  |  | X | X |  |
| Satisfaction with Intervention |  |  |  |  | X |  |
| Pregnancy Question | X** | X** | X** | X** | X** |  |

* depending on condition randomized to, each subject will complete either the CC or IC questions

** asked to women of child bearing potential only

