### 3. Study design

The study is randomized control trials that will be used to determine the efficacy of having patients utilize the asthma module of the interactive website to improve asthma control. Subjects will be randomized to either the intervention (asthma module) or control (preventive module) at the baseline visit.

Overall, the intervention is an interactive website. The website is designed to encourage patients to ask specific questions during visits with their asthma care provider that will help to improve the quality of their care and asthma control. IC subjects will use the asthma module of the interactive website for 12 months, which includes web-based asthma feedback, based on patient self-report. The feedback suggests questions to ask during visits with asthma care providers, reasons for asking the questions and links to other trustworthy websites that support the message. The website will be used a) each month and b) before visits with asthma care providers. When using the website routinely each month, the subject will report on their asthma control as well as clarify the date of their next asthma care provider visit. This allows the website to remind patients to use the website before doctor visits as well as to suggest that patients make a sooner visit, in keeping with the 2007 NAEPP Guidelines (page 345), if their asthma is not controlled and their next scheduled visit is far in the future.

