Analysis of main outcome: Data analysis will focus on the primary hypotheses that significantly more subjects in the IC will have their asthma controlled, an Asthma Control Test (ACT) score of ≥ 20, than subjects in the CC. This dichotomized version of the ACT at 12 months is the primary outcome. We considered powering on a numerical change in the Asthma Control Test (ACT), our main outcome measure, but chose not to do this as there is less consensus about what represents a meaningful change in the ACT than there is about what represents appropriate asthma control 5,98. Logistic regression will be used to analyze asthma control at 12 months. Logistic regression allows for inclusion of the two dichotomous strata. Also, it is possible that the groups may have differences at baseline in potential confounders (e.g. socio-economic status, asthma symptoms) that may contribute to group differences in the 12 month event rate between the two conditions. Logistic regression permits inclusion of these potential confounders as covariates. Additionally, as the ACT is measured every 3 months, the logistic regression model can be extended using the generalized estimating equations (GEE) approach of Zeger and Liang (1986) with a logit link so that the repeated measures on each subject can be included in the analyses 137. Thus, asthma control can be examined at any of the preceding time points as well. Tests of the primary hypotheses about intervention effects will be formulated directly in terms of the main effect of intervention. We will also assign a create variables for physicians’ practices, so that physicians who practice together will be given the same variable number. In our analyses we first perform intent-to-treat (ITT) analyses and then will perform analysis including physician- and practice-level variables, while accounting for clustering.

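### Allocation is triggered by the authorisation form and does not wait for the online baseline survey, so the only baseline ACT may be collected after randomisation and may be absent for some randomised subjects

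*Protocol*

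**What the plan says.** Section III.5 (Procedures to be followed) describes a phone screen with verbal consent, then a first login. Subjects are told that "upon logging into the application for the first time, they will have to read, review, and electronically agree to a Member Authorization Form". Refusers are excluded. For the rest: "Those that do agree will then be randomized automatically, according to an algorithm written in the management module". Later in the same section: "At baseline, 6 months, and 12 months, they will be asked to complete specific measures online, as outlined below".

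The phone screener covers "basic demographic information, race and ethnicity, exclusion criteria questions, contact information" and payment details. It contains no ACT. The schedule table in III.5 lists the ACT at baseline, cycle 6 and cycle 13 only. The same baseline column holds the pre-use questions for both the control condition (CC) and the intervention condition (IC).

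Section III.3 (Study design) gives the only other statement on timing: "Subjects will be randomized to either the intervention (asthma module) or control (preventive module) at the baseline visit". It does not say whether the survey or the allocation comes first, and III.5 describes no visit, only a phone call and logins.

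**The concern.** A baseline measure earns its place in a randomised comparison because allocation cannot have influenced it. That is secured by collecting it, or at least fixing it, before allocation is made or shown. Here the trigger for allocation is agreement to a form, and the form comes before any online measure.

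Two things are at stake. First, the ACT is self-reported, and the two modules differ openly in subject matter: asthma in one, preventive services in the other. A subject who has seen which module was assigned may answer asthma questions differently. Second, completing the survey is not a condition of randomisation, so a subject can be randomised, leave, and have no baseline ACT.

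**Working it through.** **1. The plan's own sample size.** Inputs from section III.7: 55% v 70% controlled, two-sided alpha 0.05, power 80%, 20% loss. I assume 1:1 allocation and no continuity correction.

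n per arm = [1.960·√(2·0.625·0.375) + 0.842·√(0.55·0.45 + 0.70·0.30)]² / 0.15² = 162.3, rounded up to 163. Total 326. Then 326 / 0.80 = 407.5, rounded up to 408. Both stated figures reproduce, and neither depends on when baseline is measured. Planned losses: 408 − 326 = 82.

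**2. Order of procedures.**

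| Step | Source | ACT collected? |
|---|---|---|
| Phone screen, verbal consent | III.5 and schedule | No |
| First login, authorisation form | III.5 | No |
| Automatic randomisation | III.5 | No |
| Online baseline measures | III.5 and schedule | Yes, for the first time |
| Arm-specific pre-use questions, in the baseline column | Schedule | Needs allocation to exist |

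No sentence puts survey completion between the second and third rows. The last row shows that allocation happens at some point within baseline. It does not show that the ACT comes after it.

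**3. Could baseline be missing?** Reading the bracketed numbers in the schedule as item counts, the common baseline instruments have 14 + 5 + 11 + 14 + 19 + 5 + 2 + 29 + 5 + 8 = 112 items. The arm-specific set adds 16 (IC, total 128) or 27 (CC, total 139). Subjects may skip items (Safeguards and Confidentiality). The $25 payment depends on completing the survey (III.12); randomisation does not. Missing baselines are therefore possible. No rate is given.

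**4. Where baseline ACT enters the analysis.**

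- *No-change analysis* (III.7, Differential dropout and attrition): subjects lost to follow-up keep their baseline control status. Anyone without a baseline ACT cannot be handled by this rule.
- *Change in ACT as a continuous variable* (III.7): needs baseline directly.
- *Comparison of arms at baseline, and of completers with those lost* (III.7): the second comparison uses baseline asthma control by name.
- *Adjusted models* (III.7): covariates enter only if the groups differ. Asthma symptoms are named as an example; the ACT is not.
- *Unadjusted logistic regression of 12-month control on available data*: does not use baseline ACT.

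**5. Illustrations (all rates and shifts assumed).**

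- Missing baseline in 2%, 5% or 10% of 408 gives 8, 20 or 41 subjects. If all were also lost to follow-up, that is 8/82 = 10%, 20/82 = 24% or 41/82 = 50% of the planned losses.
- Change contrast = (12-month IC − CC) − (baseline IC − CC). A shift of d points in one arm's reported baseline moves the contrast by d in full, so 0.5 points moves it by 0.5. A baseline-adjusted model passes on d times the baseline slope.
- No-change contrast with 20% loss in each arm = 0.80 × (12-month difference among completers) + 0.20 × (baseline difference among those lost). With 70% v 55% and equal baselines, this is 0.80 × 15 = 12 percentage points. A reporting shift of 5 points in baseline control would move it by 0.20 × 5 = 1 point, in either direction.

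**The case against.** The best defence is that the order within the first login is inferred. Section III.5 is not strictly chronological: just after the randomisation sentence it returns to the coordinator entering screening data from the earlier phone call. The sentence on measures at three time points is a general schedule and need not be the next step. Being allocated by an algorithm is also not the same as being shown the arm; nothing says the module is displayed before the common instruments. The ACT asks about the past four weeks, which leaves reporting as the main route for any influence within that session. All of this stands, and it is why the point is worded as what may happen. It does not supply a rule that the survey comes first, and an implementer following III.5 would build the trigger on the form.

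Several stronger readings are tempting and are not supported:

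- *That baseline ACT is shown to be unblinded.* The text does not establish when the arm becomes visible.
- *That some randomised subjects will certainly have no baseline.* Completion is paid and no rate is given.
- *That the plan contradicts itself by stratifying on ACT.* Section III.7 says "Logistic regression allows for inclusion of the two dichotomous strata" but does not name the strata, and they could be phone-screener variables. Under this order ACT could not be one of them; nothing says it was meant to be.
- *That every baseline is exposed.* Age, gender, race, ethnicity and smoking come from the screener, and emergency visits and medication use come from claims reaching back two years.
- *That early leavers are uncounted.* Those without follow-up fall within the 20% loss already built into 408.

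**Conclusion.** The point holds as a gap in the order of procedures. As written, allocation follows the form and does not wait for the survey, so the only baseline ACT and the other online self-reports may be collected after allocation, possibly with the arm apparent, and may be missing for some randomised subjects. The analyses exposed are the no-change analysis, change in ACT, baseline comparisons that use the online measures, and any model adjusted for them. The no-change rule is conservative only if baseline is independent of allocation, so the exposure weakens a check that the plan relies on to support its primary result.

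A reader might infer that the primary result itself is compromised. The documents do not support that: the unadjusted 12-month analysis of available data needs no baseline ACT, and 408/326 stands. The size of the problem is unknown. The conclusion rests on reading III.5 in sequence; if the software already runs the common survey first, the remaining defect is that the protocol does not say so.

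**What to change.** Change the trigger in the management module so that allocation is generated and shown only after the common baseline survey, including the ACT, has been submitted and locked. Present the IC and CC pre-use questions after that. Then reconcile the text: III.3 and III.5 should state the same order, and the schedule should separate the common baseline instruments from the arm-specific questions. At present the footnote mark for the arm-specific questions appears only on the 30-day cells. If the software already works this way, one sentence saying so is enough.

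The cost is a small software change and a short protocol edit, with no effect on the sample size. The downside is that a few consenting people who do not finish the survey are never randomised. Stratifying on baseline ACT would then become possible, but it is an optional design choice and not part of the correction.

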### Inclusion/exclusion criteria

In order to be eligible for the study, all patients must:

1) be between 21 and 60 years of age

2) have evidence of physician-diagnosed asthma, including at least one documented asthma-related medical encounter in the past year AND at least 3 months of asthma-related medications in the past year.

3) have self-reported asthma, based on questions from the National Asthma Survey from the Centers for Disease Control (CDC) 9.

4) speak and read English fluently

5) have access to the Internet at home or at work

6) not have a history of more than 20 pack-years of cigarette smoking.

7) be enrolled in a Highmark health plan .

8) not currently pregnant

No children will be included in the proposed. While this work is important to do, we believe that the costs of running two parallel studies (two entirely different websites and recruitment strategies) would not outweigh the additional knowledge learned, at least at this time. As the studies that informed the creation of the intervention only included adults 24,27,28,90, a significant amount of development work would need to be done that would likely result in very different interventions for adults and children. If this approach is successful, future studies could extend these findings by developing interactive websites for children, who, on average, have higher rates of Internet access 83, or for their parents to use.

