
Preliminary data analysis plan: All analyses will be conducted using SAS Version 9. Initially, descriptive statistics such as the minimum, maximum, range, median, quartiles, mean, and standard deviation for each continuous variable and frequencies and percentages for each categorical variable will be used to summarize all variables as well as detect outliers, data entry mistakes, and missing values. These descriptives will be used to “clean” the data prior to analysis. Exploratory graphical techniques will be used to further examine these data. The normality of the distribution of mediators of interest, both in their original and transformed state (if necessary), will be examined with a normal probability plot when applicable. Longitudinal plots will be used to identify trends over time that are both population- and individually-based.

Differential dropout and attrition: Initially, the two randomized groups will be compared on important demographic and other baseline variables to ensure successful randomization. If it is determined that the groups, by chance, are significantly different on some measures, we will include those theoretically meaningful confounders as covariates in subsequent analyses. T-tests, ANOVA, and/or chi-square tests of independence comparing those who complete the study with those lost to follow-up will be performed on baseline demographic variables, asthma control, asthma-related quality of life, and baseline use of controller medications to identify potential differential dropout. These comparisons ensure equality of intervention and comparison groups after accounting for study attrition. For the primary outcome, we will apply intention to treat (ITT) principles with all available data included in the first set of analyses 134. Second, subjects lost to follow-up will be conservatively assumed to have not changed their level of asthma control between baseline and 12 months. Similar findings between both approaches would increase confidence in the results overall.

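### Women who report pregnancy after randomisation are withdrawn from the whole study, so their 12-month ACT goes missing by protocol order, in tension with the intention-to-treat principle

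*Protocol*

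**What the plan says.** Pregnancy is first an entry criterion: the list under Inclusion/exclusion criteria requires that subjects are "not currently pregnant". Section III.5 (Procedures to be followed) then places randomisation at first login, after the health plan's authorisation form is accepted: "Those that do agree will then be randomized automatically, according to an algorithm written in the management module". The monthly cycles come after that. Each one puts a pregnancy question to women who could become pregnant, and the rule is: "if they state that they are, they will be withdrawn from the study". The schedule table in that section puts the pregnancy question at every contact, including Cycle 6 and Cycle 13, where the ACT is also collected.

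Outcomes are gathered by online self-report: "At baseline, 6 months, and 12 months, they will be asked to complete specific measures online". Under Analysis of main outcome in section III.7, ACT ≥ 20 is the criterion, and "This dichotomized version of the ACT at 12 months is the primary outcome".

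On the analysis, the paragraph on differential dropout and attrition in section III.7 says: "For the primary outcome, we will apply intention to treat (ITT) principles with all available data included in the first set of analyses". It adds a second analysis in which subjects lost to follow-up keep their baseline control status.

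On claims, section III.5 provides that the health plan supplies claims data on everyone enrolled.

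**The concern.** Intention to treat has two parts: subjects are analysed in the arm to which they were randomised, and they are followed up whatever happens afterwards. The withdrawal rule cuts into the second part. It ends participation because of an event after randomisation, by order of the protocol and not by the subject's own choice. The primary outcome is a five-item questionnaire answered online, so the value could still be collected at almost no burden.

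What is at stake is avoidable missing primary-outcome data, and some ambiguity about how these cases are counted. The protocol does not say whether a pregnancy withdrawal is a loss to follow-up, or whether it sits inside the 20% allowance. Nor does it say whether an ACT given at Cycle 13 counts if pregnancy is reported at that same contact. A later analysis plan cannot repair this, because it cannot recover an ACT that was never collected.

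**Working it through.** **Passages side by side (all protocol)**

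1. Randomisation happens at first login and the pregnancy check is repeated monthly afterwards (III.5). The rule therefore acts on randomised subjects.
2. The rule names the study, not the website module. No section describes outcome collection after withdrawal. Loss of the 12-month ACT is thus a clear implication of the text, not an explicit statement.
3. The intention-to-treat sentence (III.7) covers the data available. It does not promise a 12-month value for every randomised subject.
4. The second analysis (III.7) would keep these women in their arm at baseline status, but only if they count as lost to follow-up. The text does not settle this.
5. Claims (III.5) are requested for all enrolled subjects. Emergency visits, medication use and adherence, and outpatient visits come from claims, so they are not removed.

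**The plan's own sample size**

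Inputs (III.7): 55% against 70%, two-sided alpha 0.05, power 80%, 20% loss. Equal allocation is assumed, because the ratio is not stated.

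n per arm = [z(0.975)·√(2·p̄·q̄) + z(0.80)·√(p₁q₁ + p₂q₂)]² / (p₂ − p₁)²

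With p̄ = 0.625, this is [1.960·√0.46875 + 0.842·√0.4575]² / 0.0225 ≈ 162.3, so 163 per arm and 326 in total. Then 326 / 0.80 = 407.5, so 408. The stated 408 and 326 reproduce, and power at 163 per arm is 80.2%.

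**How many women could be affected**

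The documents give no figures for this, so all three inputs are assumptions: 60–70% women, 50–60% of them of childbearing potential, and 3–6% pregnant during the year.

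- Low: 408 × 0.60 × 0.50 × 0.03 = 3.7
- High: 408 × 0.70 × 0.60 × 0.06 = 10.3

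That is about 4 to 10 subjects, or 0.9% to 2.5% of 408. The loss allowance is 408 × 0.20 ≈ 82, so these cases would take up about 5% to 13% of it.

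**Effect on power**

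If the withdrawals fall within the 20% allowance, 326 remain for analysis and power stays at about 80%. If they come on top of it, the number analysed is 408 × (0.80 − w):

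| Extra withdrawals w | Subjects | Analysed | Power | Randomised to keep 326 |
|---|---|---|---|---|
| 1% | 4 | 322 | 79.7% | 413 |
| 2% | 8 | 318 | 79.2% | 418 |
| 3% | 12 | 314 | 78.7% | 424 |
| 5% | 20 | 306 | 77.6% | 435 |

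The assumed range of 0.9% to 2.5% corresponds to about 79% to 80% power. The 3% and 5% rows lie beyond it and are shown only as a stress test.

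**Bias**

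The direction and size cannot be computed. Both arms are asked the same question, so a large imbalance is unlikely. It cannot be taken as zero, because reports depend on monthly logins, and login frequency could differ between the two modules.

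**The case against.** The strongest case on the other side is that the rule is explicit and consistent. Non-pregnancy is an entry criterion, and participation ends when it is no longer met, in the same way in both arms. Missing outcome data is also not the same as a breach of intention to treat: no sentence moves these women out of their arm or discards data already collected. The protocol already has some cover, in the baseline-status analysis and in the extension to generalised estimating equations, which could use a 6-month ACT given before the report. The numbers are small and rest on assumed inputs.

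Most of this stands, and it limits the point. A reader might infer that the rule flatly contradicts the intention-to-treat statement. The documents do not support that, because the statement is confined to the data available. A reader might also infer that these women's claims are lost. The documents say otherwise: a woman who reports pregnancy at a monthly check has already accepted the authorisation form and been enrolled, and claims are sought for all enrolled subjects.

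What does not stand is the idea that the wording about available data settles the matter. It is the protocol itself that makes an obtainable primary outcome unavailable. The baseline-status analysis helps only if these women count as lost to follow-up, and then it assumes no change for subjects who could simply have been asked.

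**Conclusion.** The point holds as a minor one. Read as written, section III.5 causes the primary outcome to go missing for randomised women who report pregnancy, and this sits uneasily with the intention-to-treat principle in section III.7. The two sections should be reconciled.

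On the assumed rates above, about 4 to 10 of 408 subjects are affected. Power is unchanged if they are absorbed by the 20% allowance and about 79% to 80% if they are not. Bias is probably small but cannot be quantified from the documents. The reason to act is that the missing data are avoidable; nothing shows that the trial's conclusion depends on them.

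**What to change.** Leave any rule on website use as it is, and separate it from follow-up. Reconcile sections III.5 and III.7 so that they state that women who report pregnancy after randomisation:

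- remain in their randomised arm for analysis;
- are still asked for the 6- and 12-month online ACT unless they withdraw consent, with an ACT given at the same contact as the report explicitly counted;
- if the 12-month ACT is not obtained, count as lost to follow-up in the baseline-status analysis and within the 20% allowance.

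No change is needed for claims beyond a confirming clause. An optional sensitivity analysis may treat ACT values after the pregnancy report as missing. With perhaps 4 to 10 subjects it need not be more elaborate, and censoring would not suit a binary outcome at a fixed time.

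The cost is protocol wording, IRB agreement to continue surveying these women, and a few extra online surveys. No visits are added and the sample size stays at 408.
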